#### Data collection

The following data will be collected in this study. We will assign the study number to each participant and manage the data. The demographic characteristics, the conversation data (the voice data and the text information), and the clinical assessment results will be linked to the study number and separated from the identifiers such as name, address, and so on. They will be strictly stored in the server locked by password considering the possibility that the voice data might include identifiers such as names.

##### Demographic characteristics

Sex, age, diagnosis, diagnosis subtype, duration of illness, prescription, and complications will be collected from the medical records. We will also collect as much information as possible about their education, birthplace, outpatient or inpatient status, years of education, educational background, occupation, work status, employment status, income, marital status, number of years of married (or divorced or separated), number of children, number of people living together, etc. If some information is missing, the patients will be asked to provide the information.

##### Conversation data

Up to a 60-min conversation with a participating psychiatrist or psychologist will be conducted. We will confirm that the participant speaks Japanese-language as the primary. A participating psychiatrist or psychologist will avoid including the participant's identifiers in the recorded part of the conversation as much as possible. The conversation consists of three parts: free conversation, picture-description task, and story-telling task. During free conversation, a participant speaks with a psychiatrist or psychologist about the course of the illness, the patient's current condition, daily life, sleep patterns, interests and hobbies, and comments on news, movies, stories, and pictures, etc. No strict structuring is performed. During picture-description task, participants are presented with three pictures: one depicting three children eating donuts used in Visual Perception Test for Agnosia (VPTA), one showing the waterside used in COGNISTAT and one representing the shore used in WAB. The patients are asked to explain them in as much detail as possible. Pictures are presented in the same order to all participants. In story-telling task, participants are asked to describe the story of Cinderella in as much detail as possible. For example, a psychologist or a psychiatrist asks them, “Please think about how you would explain the story to someone who does not know the story.” If the participant does not know the story of Cinderella, the famous Japanese folktale “Kaguya-Hime” is used instead. The picture-description task and story-telling task each take about 10 min. In all the conversations, an interviewer is required to ask questions using neutral words, not using emotional-valenced words, to make an interjection, and to dig into the participant's story. The interviewer and participant are asked to wear microphone headsets named PRO8HE (39) (its range of the frequency of sampling is from 200 to 18,000 Hz, and its sensitivity is −55dB.), and the conversation is audio-recorded in a consultation room or similar quiet environment.

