#### Participants

This study is a multicenter, prospective, observational study. Subject recruitment was started in 2018 and is ongoing. Participants are being recruited at seven hospitals and three outpatient clinics in Japan. Patient recruitment is being conducted at the following locations and hospitals: Tokyo (Keio University Hospital, Tsurugaoka Garden Hospital, Oizumi Hospital, Komagino Hospital, Oizumi Mental Clinic, Asakadai Mental Clinic), Kanagawa (Nagatsuta Ikoinomori Clinic), Shiga (Biwako Hospital), Yamagata (Sato Hospital), and Fukushima (Asaka Hospital). Participants are inpatients or outpatients aged ≥20 years who meet the diagnostic criteria for depression, bipolar disorder, schizophrenia, anxiety disorder (including obsessive-compulsive disorder), mild cognitive impairment, or dementia according to the DSM-5 or ICD-11. Healthy volunteers will consist of healthy individuals with no history of psychiatric disorders who have volunteered to participate in the study after reading the research group's website and printed recruitment advertisements and who are at least 20 years old at the time of consent. Researchers will obtain written informed consent about participation in this study and data storage from all the participants. In cases where the patients are judged to be decisionally impaired, the patients' guardians will be asked to provide consent. Participants will be able to leave the study at any time. This study was approved by the Institutional Review Board of Keio University School of Medicine and the participating medical facilities.

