			**Number of visits**				
			**1**	**2**	**3**	**4**	**5**
			**Assessments must be done in Visit 1 and Visit 2**		**Assessments will be done as long as possible**		
A) Demographic characteristics	All participants	Demographic characteristics	✓				
		Information on treatment history	✓	✓	✓	✓	✓
	Only patients	SCID-IV-TR	✓ (Once during research period)				
B) Conversation with a psychiatrist or psychologist	All participants	free conversation, picture-description task, and story-telling task	✓	✓	✓	✓	✓
C) Severity assessment using clinical rating scales	C-1) Monopolar depression disorder or Bipolar disorder or Anxiety disorder	HAM-D MADRS YMRS HAM-A STAI SWLS Cantril's Ladder of life scale FS-J Subjective Well-being Inventory	✓	✓	✓	✓	✓
	C-2) Schizophrenia	PANSS SWLS Cantril's Ladder of life scale FS-J Subjective Well-being Inventory	✓	✓	✓	✓	✓
	C-3) Neurocognitive disorder	MMSE CDR MoCA-J WMS-R LM SWLS Cantril's Ladder of life scale FS-J Philadelphia Geriatric Center Morale Scale Subjective Well-being Inventory	✓	✓	✓	✓	✓
	For healthy volunteers	*MMSE (*: Performed before all of the other tests)	✓				
		All of C-1), C-2), C-3)	✓	✓	✓	✓	✓

FS-J, The Japanese version of the Flourishing Scale; SWLS, Satisfaction With Life Scale, SCID, Structural Clinical Interview for DSM-5; HAM-D, Hamilton Depression Rating Scale; MADRS, Montgomery-Asberg Depression Rating Scale; YMRS, Young Mania Rating Scale; STAI, State-Trait Anxiety Inventory; PANSS, Positive And Negative Syndrome Scale; MMSE, Mini-Mental State Examination; MoCA-J, Montreal Cognitive Assessment-Japanese version; WMS-R LM, Wechsler Memory Scale-Revised Logical Memory; CDR, Clinical Dementia Rating; M.I.N.I., Mini-International Neuropsychiatric Interview.

Healthy volunteers will be screened using the Mini-International Neuropsychiatric Interview (M.I.N.I.) and the Mini-Mental State Examination (MMSE). They will be excluded if they have a history of psychiatric disorders or cognitive impairment. For the M.I.N.I., if any diagnosis is found, and for the MMSE, if the score is below 27, the participant will not be allowed to participate in the study as a healthy subject.

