#### Data processing and annotation

The acquired voice data will be converted into text information using speech recognition technology developed by the research group and will be compensated manually; annotations, such as pauses, fillers, nods, interjections, repetitions, co-supplementation, lexical responses, incomplete sentences, misstatements, etc., will also be made. We will mask the part of personal identifiers such as names when converting voice data into text information. At the same time, the following phonic information will be extracted from the recorded audio data to utilize the physical properties of the audio data in the machine learning model: fundamental frequency (F0); first, second, and third formant frequencies (F1, F2, F3); cepstral peak prominence (CPP); and Mel-frequency cepstrum coefficients (MFCC). These are the major features in speech-language analysis (40). Software such as Praat (41) and openSMILE (42) will be used to extract such phonic information.

Based on the annotated text data thus obtained, various variables are calculated using NLP techniques, such as morphological and syntactic analyses using MeCab (43, 44) and JUMAN (45, 46). For instance, these analyses will include the frequency of the occurrence of each part of speech, vocabulary (negative and positive words), syntactic complexity, length of the utterance, frequency of occurrence of person, use of pronouns and distance to the referent, use of case structure (“te, ni, wo, ha”), and so on. We will use NLP techniques to represent textual data as n-grams and word embeddings obtained from pre-trained models such as BERT (47).

Linguistic features considered to be characteristic of specific psychiatric diseases will be selected and statistically compared between groups (e.g., patients vs. healthy subjects, patients in different disease groups). This step is necessary to verify whether each variable has pathological validity before using it for machine learning.

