### Machine learning

The machine learning models in this study will be trained to perform the following tasks: (1) to predict whether a subject has or does not have psychiatric disorders such as depression, bipolar disorder, anxiety disorder, schizophrenia, or dementia; (2) to predict the severity of a subject's state based on the results of rating scales such as the Hamilton Rating Scale for Depression (HAM-D), the Young Mania Rating Scale (YMRS) for bipolar disorder, the Positive And Negative Syndrome Scale (PANSS) for schizophrenia, and MMSE for dementia; (3) to predict the improvement or deterioration of a subject's disorder with respect to a previously recorded state if the subject has undergone a prior assessment; and 4) to predict the scores of individual items in clinical rating scales that are indicators of different aspects of a subject's disorder, such as positive symptoms, negative symptoms, and disorganized symptoms for schizophrenia. The data used to train these machine learning models may include voice features extracted from voice data obtained from subjects, conversational and linguistic information from transcribed text data, and annotations assigned to the data described above.

Next, we will need to perform feature engineering and design the architecture of machine learning. The data, represented through NLP techniques, together with the features obtained through feature engineering processes, will be then used to extract disease features. In particular, disease features extraction will be performed relying on machine learning models such as decision trees, support vector machines (SVM), and deep learning architectures. Each model will be evaluated using cross-validation and then the relative importance of each feature will be estimated using a feature importance estimation method such as XGBoost. We will then evaluate the results using the mean absolute error, coefficient of determination, and correlation coefficients. We also plan to verify whether the features obtained in this manner can distinguish firstly between a normal and disease state, secondly among different diseases, and whether they can distinguish changes in disease severity over time.

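### Free conversation covers illness topics that healthy controls lack by design, so content-bearing text features from it can let the patient-versus-healthy model recognise illness talk rather than disordered language

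*Protocol article*

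**What the plan says.** The Conversation data section divides each recording into free conversation, a picture-description task and a story-telling task. In the free part "a participant speaks with a psychiatrist or psychologist about the course of the illness" and about the patient's current condition, followed by topics open to anyone, such as daily life, sleep, hobbies and news. On topic control it says "No strict structuring is performed". For the other two parts, "The picture-description task and story-telling task each take about 10 min", and every participant sees the same pictures in the same order. Table 1 schedules all three parts for all participants at every visit.

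Under Participants, controls are "healthy individuals with no history of psychiatric disorders". The note under Table 1 on M.I.N.I. and MMSE screening adds: "They will be excluded if they have a history of psychiatric disorders or cognitive impairment".

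Under Data processing and annotation, names and similar identifiers are masked during transcription; no other masking is stated. The text is analysed for vocabulary, among other features, and the plan will "represent textual data as n-grams and word embeddings obtained from pre-trained models such as BERT". Under Machine learning, Task 1 predicts presence or absence of a disorder, the features are later to be checked for telling diseases apart, and the possible inputs include "conversational and linguistic information from transcribed text data".

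**The concern.** The first topics listed for free conversation are ones a patient has and a control lacks by definition. N-grams, vocabulary measures and embeddings carry subject matter, such as the name of a diagnosis, a drug, a hospital admission or a symptom. A classifier given these features can do well by detecting that the speaker is talking about being ill.

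The stated aim is to quantify the linguistic features of these disorders and build objective biomarkers from them. If part of the reported accuracy comes from topic, it does not measure loosening of associations, inhibition or any other disturbance of language, and it may not carry over to settings where illness is not discussed. The same route may exist between diseases, because a patient recounting an illness may name it.

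**Working it through.** **1. Does the route exist in the text?** Four statements are needed, and all are present:
- the free part includes illness course and current condition, without fixed structure (Conversation data);
- controls have no psychiatric history (Participants; note under Table 1);
- masking covers personal identifiers only (Data processing and annotation);
- transcripts become content-bearing features and may be inputs to Task 1 (Data processing and annotation; Machine learning).

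**2. Does a stated safeguard close it?**
- Neutral question wording limits the emotional tone of the interviewer, not the topic.
- The group comparison meant to establish pathological validity looks for differences between groups. A topic-driven feature also differs between groups, so it would pass.
- Cross-validation tests on held-out records from the same interviews. The topic difference is present in every fold.
- The picture and story tasks give all groups a common subject, but nothing makes them a separate or main input.

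**3. How much of the recording is free conversation?** The Abstract gives 30 to 60 minutes in all, and the two tasks take about 10 minutes each. 30 − 20 = 10 minutes (10/30 = 33%); 60 − 20 = 40 minutes (40/60 = 67%). This is the share of all free conversation. The share spent on illness is not given.

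**4. What could topic alone achieve?** No figure in the plan depends on this point: the sample size of about 1,000 reproduces as 10 cases × 100 variables and is not affected. For illustration, let π be the share of patients, q the proportion of patients and r the proportion of controls whose free conversation mentions an illness of their own. The rule that a mention means patient has

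accuracy = π·q + (1 − π)·(1 − r).

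π = 20/30 comes from the pilot (Sample size). q and r are assumptions; the article gives neither.

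| q | r = 0 | r = 0.10 | r = 0.20 |
|---|---|---|---|
| 0.6 | 0.733 | 0.700 | 0.667 |
| 0.7 | 0.800 | 0.767 | 0.733 |
| 0.8 | 0.867 | 0.833 | 0.800 |
| 0.9 | 0.933 | 0.900 | 0.867 |

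Worked cell: q = 0.7, r = 0.10 gives (2/3)(0.7) + (1/3)(0.9) = 0.467 + 0.300 = 0.767. For comparison, the pilot reported 72–80%, the target is 90%, and calling everyone a patient gives 20/30 = 67%.

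**5. Would cross-validation show it?** Data were simulated with 400 records in two equal groups and 20 language features that do not differ between the groups. A linear classifier was assessed by 5-fold cross-validation over 50 repetitions. Mean accuracy was 0.50 without a topic indicator, 0.80 with one at q = 0.7, r = 0.1, and 0.90 with one at q = 0.9, r = 0.1. The formula with π = 0.5 gives the same: (0.7 + 0.9)/2 = 0.80 and (0.9 + 0.9)/2 = 0.90. Cross-validation reports the topic effect as genuine performance.

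**The case against.** The strongest reply is that the plan does not fix which text feeds which model. The Machine learning section lists inputs that may be used, and an article can leave the choice of segment to a fuller document. It is also true that many listed features are not about topic: part-of-speech frequencies, syntactic complexity, timing, fillers and acoustic measures are less exposed, and the pilot features described are mostly of this kind. Both points stand and limit the concern to content-bearing features. They do not remove it, because the topics, the definition of controls, the masking rule and the text representation are all stated, and together they open the route.

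A second fair point is scientific. Loosening of associations and flight of ideas may show best in unconstrained speech, so making the structured tasks the only input would have a cost. That is a reason to keep free conversation and report it separately.

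A reader might also infer several stronger things that the article does not support:
- That illness words would separate the groups almost completely. No figure shows this. The pilot reached 72–80%, and it does not say which part of the interview it used.
- That one to two thirds of the recording is illness talk. That range is all free conversation, much of it on shared topics.
- That severity prediction is contaminated in the same way. A patient's description of current symptoms is relevant to a symptom rating, and severity models can be fitted among patients alone.
- That early detection in undiagnosed people is defeated as the study's aim. The Introduction and Discussion mention it as a future possibility; the Aim concerns diagnosis and severity.
- That unblinded interviewers, or the substitution of Kaguya-Hime for Cinderella, bias the result. The article does not mention interviewer blinding, and it gives no frequency for the substitution and no link to diagnosis, age or memory.

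**Conclusion.** The concern holds for n-grams, embeddings and vocabulary features taken from free conversation, in the patient-versus-healthy model, and possibly in the comparison between diseases. Such features can let a model recognise illness talk, and the checks in the plan would not reveal it. The documents establish the route, not its size. The accuracies above show only that topic could by itself give values in the range of the pilot and the target under assumed mention rates; they are not estimates of what happened or will happen. The disease-versus-disease part is an inference from patients being able to name their own condition, and no figure supports it.

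**What to change.** For content-bearing features in Task 1 and in the disease-versus-disease comparison:

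1. Use the participant's speech only.
2. Report performance separately for the picture and story tasks and for free conversation.
3. In free conversation, mask or remove diagnosis, drug, admission and symptom words, or restrict the text to topics shared by all groups. Report the difference from the unmasked result.
4. Add a topic-only baseline, so that readers can see how much accuracy subject matter gives by itself.
5. Rest the claim that linguistic features of the disorders were quantified on the common-task or masked results.

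No new data collection is needed, because the common tasks are already scheduled at every visit. The cost is the work of segmenting and masking transcripts, less text per record, and possibly a lower headline accuracy.

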##### Clinical assessment

The severity of the illness will be assessed using the rating scales described in the table (Table 1). In addition, the treating psychiatrists will be asked to evaluate each patient's current disease severity using the Clinical General Impression Scale-Severity (CGI-S). A structured psychiatric diagnostic interview (SCID-IV-TR) will be conducted to the greatest degree feasible to confirm the diagnoses during the follow-up interview.

**Table 1 T1:** Data collection and visit schedule.

			**Number of visits**				
			**1**	**2**	**3**	**4**	**5**
			**Assessments must be done in Visit 1 and Visit 2**		**Assessments will be done as long as possible**		
A) Demographic characteristics	All participants	Demographic characteristics	✓				
		Information on treatment history	✓	✓	✓	✓	✓
	Only patients	SCID-IV-TR	✓ (Once during research period)				
B) Conversation with a psychiatrist or psychologist	All participants	free conversation, picture-description task, and story-telling task	✓	✓	✓	✓	✓
C) Severity assessment using clinical rating scales	C-1) Monopolar depression disorder or Bipolar disorder or Anxiety disorder	HAM-D MADRS YMRS HAM-A STAI SWLS Cantril's Ladder of life scale FS-J Subjective Well-being Inventory	✓	✓	✓	✓	✓
	C-2) Schizophrenia	PANSS SWLS Cantril's Ladder of life scale FS-J Subjective Well-being Inventory	✓	✓	✓	✓	✓
	C-3) Neurocognitive disorder	MMSE CDR MoCA-J WMS-R LM SWLS Cantril's Ladder of life scale FS-J Philadelphia Geriatric Center Morale Scale Subjective Well-being Inventory	✓	✓	✓	✓	✓
	For healthy volunteers	*MMSE (*: Performed before all of the other tests)	✓				
		All of C-1), C-2), C-3)	✓	✓	✓	✓	✓

FS-J, The Japanese version of the Flourishing Scale; SWLS, Satisfaction With Life Scale, SCID, Structural Clinical Interview for DSM-5; HAM-D, Hamilton Depression Rating Scale; MADRS, Montgomery-Asberg Depression Rating Scale; YMRS, Young Mania Rating Scale; STAI, State-Trait Anxiety Inventory; PANSS, Positive And Negative Syndrome Scale; MMSE, Mini-Mental State Examination; MoCA-J, Montreal Cognitive Assessment-Japanese version; WMS-R LM, Wechsler Memory Scale-Revised Logical Memory; CDR, Clinical Dementia Rating; M.I.N.I., Mini-International Neuropsychiatric Interview.

Healthy volunteers will be screened using the Mini-International Neuropsychiatric Interview (M.I.N.I.) and the Mini-Mental State Examination (MMSE). They will be excluded if they have a history of psychiatric disorders or cognitive impairment. For the M.I.N.I., if any diagnosis is found, and for the MMSE, if the score is below 27, the participant will not be allowed to participate in the study as a healthy subject.

In this study, not only the collection of linguistic information associated with each disease but also the relationship between illness severity and linguistic information will be important. Therefore, we will follow the participants two to five times during the study period to interview the subjects at times when the severities of their symptoms differ (i.e., severe, moderate, mild, and during remittance). An interval of at least 1 month between the two assessments will be required. The same procedures described above will be conducted for the follow-up data collection.

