**Methods:**

This study will have a multi-center prospective design. The DSM-5 or ICD-11 criteria for major depressive disorder, bipolar disorder, schizophrenia, and anxiety disorder and for major and minor neurocognitive disorders will be regarded as the inclusion criteria for the psychiatric disorder samples. For the healthy subjects, the absence of a history of psychiatric disorders will be confirmed using the Mini-International Neuropsychiatric Interview (M.I.N.I.). The absence of current cognitive decline will be confirmed using the Mini-Mental State Examination (MMSE). A psychiatrist or psychologist will conduct 30-to-60-min interviews with each participant; these interviews will include free conversation, picture-description task, and story-telling task, all of which will be recorded using a microphone headset. In addition, the severity of disorders will be assessed using clinical rating scales. Data will be collected from each participant at least twice during the study period and up to a maximum of five times at an interval of at least one month.

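### Apart from a known history, a healthy control's cognition is cleared only by an MMSE of 27 or more at Visit 1, so the healthy and mild-cognitive-impairment labels can overlap, and the CDR already scheduled for volunteers has no stated part in the label

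*Protocol article*

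**What the plan says.** **Controls.** Below Table 1 in the Clinical assessment section, volunteers are screened with the M.I.N.I. and the MMSE. A general exclusion comes first: "They will be excluded if they have a history of psychiatric disorders or cognitive impairment". The operational rule follows. Any M.I.N.I. diagnosis excludes, and "for the MMSE, if the score is below 27, the participant will not be allowed to participate in the study as a healthy subject". The abstract likewise names the MMSE as the instrument that confirms the absence of current decline. Table 1 ticks this screening MMSE at Visit 1 only.

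**Cases.** The Participants section enrols patients with several diagnoses, including "mild cognitive impairment, or dementia according to the DSM-5 or ICD-11". No MMSE bound is attached. The abstract calls the two neurocognitive groups major and minor neurocognitive disorder.

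**Battery.** Block C-3 of Table 1 (neurocognitive disorder) begins "MMSE CDR MoCA-J WMS-R LM". Healthy volunteers receive all of C-1, C-2 and C-3 at visits 1 to 5. The column heading for the first two visits reads "Assessments must be done in Visit 1 and Visit 2"; the later visits are done where possible.

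**Use of the label.** The Machine learning section plans to verify whether the features "can distinguish firstly between a normal and disease state", before separating diseases from one another. The Data processing section compares features between patients and healthy subjects before any modelling.

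**The concern.** The case label rests on diagnostic criteria. The control label rests on one screening score plus the absence of a known history. Because the case label has no MMSE ceiling, the two definitions do not exclude each other. A volunteer with unrecognised mild impairment who scores 27 or more enters as healthy.

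In the neurocognitive-versus-healthy comparison, such a volunteer puts impaired speech into the reference class. Differences in features shrink, and a model that correctly flags the impairment is scored as making a false positive. Each participant contributes two to five recordings, so one wrong label enters the data more than once. The study already plans to hold the CDR, MoCA-J and WMS-R LM for these volunteers, yet no passage says how they bear on who counts as healthy.

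**Working it through.** **1. The definitions side by side**

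| | Healthy control | Mild cognitive impairment case |
|---|---|---|
| Basis | No known history; no M.I.N.I. diagnosis; MMSE ≥ 27 at Visit 1 | DSM-5 or ICD-11 diagnosis |
| MMSE range allowed | 27–30 | No limit stated |
| CDR, MoCA-J, WMS-R LM | Scheduled, no stated role in the label | Scheduled as severity ratings |

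The MMSE ranges intersect at 27–30. The history exclusion removes only known cases if it refers to history. If the sentence is read as also excluding current impairment, the only means given for detecting it is the same MMSE cut-off. The abstract assigns the M.I.N.I. to psychiatric history. Overlap is therefore possible from the definitions alone, without any outside fact about MMSE scores in mild impairment.

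**2. Size (assumed inputs)**

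The plan states no figure that depends on this rule, so there is none to reproduce. It gives no prevalence of unrecognised impairment, no MMSE pass rates and no age distribution for controls. Assumptions:

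- q, share of volunteers with unrecognised impairment: 5–20%
- m, share of those scoring at least 27: 20–60%
- h, share of the other volunteers scoring at least 27: 95%

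Mislabelled share of accepted controls: c = qm / [qm + (1 − q)h]

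- Low: 0.05 × 0.2 / (0.01 + 0.95 × 0.95) = 0.01 / 0.9125 = 1.1%
- Middle (q = 10%, m = 40%): 0.04 / (0.04 + 0.855) = 4.5%
- High: 0.20 × 0.6 / (0.12 + 0.80 × 0.95) = 0.12 / 0.88 = 13.6%

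**3. Effect on a feature difference**

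If mislabelled controls speak like cases, the observed mean difference is (1 − c) times the true one, which is a shrinkage of 1.1–13.6%.

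**4. Effect on specificity**

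Take a classifier with true sensitivity and specificity of 90%. Apparent specificity = (1 − c) × 0.9 + c × 0.1.

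- Low: 89.1%
- Middle: 86.4%
- High: 79.1%

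The loss is c × (sensitivity + specificity − 1) = 0.8c, or 0.9 to 10.9 percentage points. If the model detected mild impairment only half the time, the loss would be 0.4c, or 0.4 to 5.5 points.

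**5. Number of controls**

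The Discussion lists 102 + 89 + 58 + 35 + 79 = 363 patients among more than 400 participants. The control count is not given. If the total were exactly 400 and everyone unlisted were a control, there would be 37. The range in step 2 then corresponds to about 0.4 to 5 people.

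**The case against.** - **The MMSE is not the only safeguard.** This stands. The history exclusion also applies, although it offers no second test of current cognition.
- **Silence is not disregard.** A reader might infer that the CDR, MoCA-J and WMS-R LM results are deliberately ignored, or that a control who declines always stays labelled healthy. The article does not say so, and handling of later changes may sit in a fuller document. What stands is narrower: the article does state the control rule, with instrument and cut-off, and that rule leaves the overlap open.
- **Actual overlap is not shown.** A reader might infer that mild impairment commonly scores 27–30, or that identical scores make a patient a case and a volunteer a control. The document supports neither. It gives no score distribution, and patients enter by diagnosis, not by CDR or memory score. Only possible overlap is established.
- **The harm is limited.** A reader might extend it to every disease-versus-healthy model or to the early-detection aim. The mechanism concerns neurocognitive features. Task (1) in the Machine learning section names dementia, not mild impairment, and the Discussion's early-detection paragraph refers to psychiatric disorders and untreated psychosis. The point bears mainly on the neurocognitive-versus-healthy contrast, since mild impairment is enrolled as a case group.
- **Stricter controls carry their own risk.** Reapplying MMSE ≥ 27 at every visit would drop some healthy people through retest variation, and removing borderline controls can make accuracy look better than it is. Both objections stand and shape the fix.

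**Conclusion.** The point holds as a weakness in a stated rule: the healthy and neurocognitive definitions are not mutually exclusive, and data already scheduled could separate them better. It is worth correcting, but it does not undermine the study as a whole.

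Its size cannot be derived from the document. The range of 1.1–13.6% mislabelled controls rests wholly on the assumed inputs, and the low end is close to trivial. The apparent specificity of 89.1% down to 79.1% also assumes that the model detects mild impairment with 90% sensitivity. Since controls need only be aged 20 or over, the share depends heavily on how many are old enough for unrecognised impairment to be plausible, which the article does not report.

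**What to change.** 1. Keep MMSE ≥ 27 and the history exclusion for entry.
2. For the neurocognitive-versus-healthy comparison, count as healthy only controls with a global CDR of 0 at Visit 1. Apply this to data already collected, and write the rule down before that comparison is analysed.
3. Report the same comparison with all MMSE-eligible controls as a sensitivity analysis.
4. In a further sensitivity analysis, drop control records from later visits with a CDR of 0.5 or more. Do not reapply the MMSE cut-off at each visit.
5. Leave the MoCA-J and WMS-R LM out of the label, since the article gives no threshold for either on which to build one.

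**Cost.** The change is one of wording plus relabelling, with no new test where the scheduled C-3 data were obtained. State how controls without a Visit 1 CDR are handled. A few control records are lost and the control group becomes somewhat cleaner than the recruited one; the all-controls analysis makes the effect of that visible.
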